## Abstract

**Background:**

Despite comprehensive guidelines for healthy gestational weight gain (GWG) and evidence for the efficacy of dietary counseling coupled with weight monitoring on reducing excessive GWG, reporting on the effectiveness of interventions translated into routine antenatal care is limited.

**Objective:**

This study aims to implement and evaluate the Living Well during Pregnancy (LWdP) program in a large Australian antenatal care setting. Specifically, the LWdP program will be incorporated into usual care and delivered to a population of pregnant women at risk of excessive GWG through a dietitian-delivered telephone coaching service.

**Results:**

Data collection of all variables was completed in December 2020, with results expected to be published by the end of 2021.

**Conclusions:**

This study will evaluate the implementation of an evidence-based intervention into routine health service delivery and will provide the practice-based evidence needed to inform decisions about its incorporation into routine antenatal care.

**International Registered Report Identifier (IRRID):**

DERR1-10.2196/27196

## Introduction

### Background

Excessive gestational weight gain (GWG) is a problem within the Australian obstetric population, occurring in 40% to 60% of pregnancies, particularly in the 50% of women already above a healthy weight prior to pregnancy [1]. This weight gain is associated with costly adverse medical and obstetric complications and contributes to the development of obesity in mothers and their offspring [2].

In Australia, comprehensive guidelines for healthy GWG from the Institute of Medicine (IOM [2]) have been widely promoted. Dietary counseling and weight monitoring have been shown to be effective in reducing GWG in research contexts and in routine antenatal care [3-5]. However, women already overweight before pregnancy are at greatest risk of excessive GWG [6], experience greater barriers to achieving a healthy weight gain, have lower confidence to achieve health goals [7], and have a need for more intensive support [8].

In addition, poor uptake of the typical clinical (face-to-face) model of dietetic counseling is seen in both research trials [9,10] and routine antenatal care services [11,12]. A face-to-face model of care to reduce GWG in overweight and obese pregnant women at our metropolitan tertiary hospital was poorly attended, and less than 10% of eligible women were referred [13,14]. Barriers to referral and engagement are likely multifactorial, with many women citing work commitments, timing, location [15], transport, and travel [16] as reasons for nonattendance.

Telephone counseling has been demonstrated as an effective and cost-effective solution for delivering positive weight management outcomes in a wide range of adult populations [17-19]. Individualized advice can be provided without requiring additional hospital visits and aligns with the preferences of women identified in formative work [20]. While various telephone-based interventions (either telephone counseling or text messages) have been trialed in the at-risk pregnant population, results have been varied, with limited reporting on the feasibility and cost-effectiveness of the approach within routine antenatal care settings [19,21]. This study aims to implement and evaluate the Living Well during Pregnancy (LWdP) program targeting pregnant women at risk of excessive GWG and delivered via telephone within the dietetic service in a large Australian tertiary setting. This program will be evaluated using metrics from the RE-AIM (Reach, Effectiveness, Adoption, Implementation, and Maintenance) framework, which includes effectiveness and implementation outcomes [22].

## Methods

### Study Design

The LWdP program will use a type 2 effectiveness-implementation hybrid design [23] to compare prospectively gathered data on participants enrolled in the LWdP program with a retrospective comparison group who was referred to the dietitian for pregnancy weight management. The setting is a tertiary metropolitan hospital that delivers approximately 4500 babies per year and offers 8 different models of antenatal care for both high- and low-risk pregnancies, including general practitioner shared care. These models of antenatal care will be consistent across the retrospective (preimplementation) and prospective (postimplementation) study periods. The retrospective control group will comprise pregnant women referred for dietetic care in the 12 months prior to the study period who meet the inclusion criteria. The prospective group will be consenting participants in the LWdP program referred for dietetic care during the 12-month study period. The RE-AIM evaluation framework will be used to understand the following about the LWdP program: reach and adoption (the number and representativeness of service referrers and participants), implementation (number of referrals, consent rates, fidelity of delivery, program completion rates, and costs of delivery), and effectiveness (maternal and neonatal outcomes) [22]. Evaluating the maintenance domain will not be possible within the time frame of the study. Ethics approval was granted from the Royal Brisbane and Women’s Hospital Human Research Ethics Committee (HREC/17/QRBW/159).

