### Screening and Consent

A waiver of participant consent was received as part of the ethics application to retrospectively access routinely collected clinical and administrative data from eligible women in the preimplementation group. For the postimplementation group, all women booked for an initial appointment in the LWdP program will be provided with an electronic link to the participant information sheet and electronic consent form with their participant workbook.

At the commencement of the program, the dietitian counsellor will discuss the evaluation process and answer any questions the participant may have. Program participants who consent to the evaluation will be requested to complete the consent form online in addition to having verbal consent recorded in their health record.

At the completion of the program, participants who verbally agreed to be involved in the evaluation but did not complete the consent form will be reminded to complete this online and a replacement link will be sent if required. Verbal consent will be documented on this second occasion. If no written consent form is received by the time of data analysis but two occasions of verbal consent are documented in the participant’s health record, consent to participate in the evaluation will be considered granted.

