#### Statistical Analysis

Primary (program implementation) outcomes (reach, uptake, and retention) will be reported descriptively and compared with the outcomes of a retrospective face-to-face comparison group. Where corresponding data are available for any secondary outcomes (such as GWG), results from the retrospective group will be compared with those of the prospective group. Chi-square and independent sample *t* tests will compare outcomes between retrospective and prospective groups. Analyses of secondary (program effectiveness) outcomes in the prospective group will be by mixed models, which will allow for repeated measures (baseline and follow-up) and include all participants with baseline data (including those with missing data at follow-up), with adjustment for predictors of dropouts to minimize selection bias. The relationship between intervention dose (number of calls received) and secondary behavioral and clinical outcomes will be examined. The optimal model will be selected using both indices of fit and model interpretability and parsimony. Outcomes will be reported as per protocol and intention-to-treat. Per protocol is defined as any participant who completed 4 or more telephone counseling sessions. Sensitivity of conclusions to missing data assumptions will be evaluated.

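### The compared groups enter by different rules, and membership of the LWdP group partly depends on completing the programme, so retention computed on consenters tends to be inflated

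*Protocol article*

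**What the plan says.** Study Design defines the two groups differently. Controls are described as follows: "retrospective control group will comprise pregnant women referred for dietetic care in the 12 months prior to the study period who meet the inclusion criteria". Nothing there requires attendance, and Screening and Consent adds that "A waiver of participant consent was received as part of the ethics application to retrospectively access routinely collected clinical and administrative data". For the programme group, "The prospective group will be consenting participants in the LWdP program referred for dietetic care during the 12-month study period".

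Screening and Consent then sets out how an LWdP woman comes to count as consenting. An electronic form goes to every woman booked for a first appointment. "At the commencement of the program, the dietitian counsellor will discuss the evaluation process and answer any questions the participant may have"; verbal consent can be recorded then. The follow-up step comes at the end: "At the completion of the program, participants who verbally agreed to be involved in the evaluation but did not complete the consent form" are reminded and sent a new link if needed, and "Verbal consent will be documented on this second occasion". The fallback is worded "If no written consent form is received by the time of data analysis but two occasions of verbal consent are documented", in which case consent is treated as given.

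Statistical Analysis compares reach, uptake and retention, as primary outcomes, with the retrospective group. Chi-square and t tests compare outcomes between the groups, including GWG where control data exist. Results are to be reported as per protocol and intention-to-treat. The mixed models for the prospective group "include all participants with baseline data (including those with missing data at follow-up") and adjust for predictors of dropout. The Results section gives 49 retrospective women and 152 consenting LWdP women.

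**The concern.** One group is assembled at referral and needs no consent. The other is assembled from women who took part and consented, and for those without a written form the deciding consent is collected only at programme completion. For that subset, completing the programme is a condition of being in the group whose completion is then measured.

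At stake is a primary comparison. An LWdP retention figure computed on consenters could exceed the control figure with no true difference. The GWG and birth-outcome comparisons use the same two groups, so they may set more engaged women against a less selected group. Adjustment for predictors of dropout works only among women already in the prospective group; it cannot restore women who never entered it. The limitations paragraph in the Discussion mentions the retrospective control in general terms but not this difference in entry.

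**Working it through.** **1. Who is included in the LWdP group** (from Screening and Consent)

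| Written form at start | Verbal consent at start | Completes programme | Included? |
|---|---|---|---|
| Yes | either | Yes or no | Yes |
| No | Yes | Yes | Yes, once the late form or second verbal consent is obtained |
| No | Yes | No | No: the second occasion does not arise |

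The last two rows differ only in completion. No such filter applies to controls.

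**2. Effect on retention.** The article states no retention rate, so there is no figure to reproduce. All rates below are assumptions for illustration. Let c be true completion, v the share of completers captured by the consent rule, and w the share of non-completers captured (in practice, those who returned the form).

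Observed completion = c·v / (c·v + (1 − c)·w)

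This exceeds c exactly when v > w. With c = 0.60 and v = 1:

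- w = 1.0: 0.60 / (0.60 + 0.40) = 60%, no bias
- w = 0.9: 0.60 / (0.60 + 0.36) = 62.5%
- w = 0.7: 0.60 / (0.60 + 0.28) = 68.2%
- w = 0.5: 0.60 / (0.60 + 0.20) = 75.0%

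The sign can reverse. With w = 1 and v = 0.9, observed completion is 0.54 / (0.54 + 0.40) = 57.4%.

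**3. Effect on the comparison.** Take 49 controls and 152 LWdP women (Results), equal true completion in both groups, v = 1, and a two-sided 5% level (assumed; the article states none). Over true completion of 40% to 70%:

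| w | Spurious gain in LWdP completion | Chance of a significant difference |
|---|---|---|
| 0.8 | 4.5 to 5.6 points | about 10% |
| 0.6 | 9.5 to 12.6 points | 29% to 34% |
| 0.4 | 15.4 to 22.5 points | 66% to 79% |

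**4. Difference in starting point.** If some controls never attended, their retention per referred woman is uptake times retention among starters. With 50% retention among starters, that is 0.5 × 0.5 = 25% at 50% uptake and 0.9 × 0.5 = 45% at 90% uptake. A group of starters would show 50%.

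**5. Effect on GWG.** Suppose c = 0.5 and v = 1, with excessive GWG in 40% of completers and 60% of non-completers. The true rate is 50%.

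- w = 0.6: (0.5 × 0.4 + 0.5 × 0.6 × 0.6) / (0.5 + 0.5 × 0.6) = 0.38 / 0.80 = 47.5%
- w = 0.4: (0.20 + 0.12) / (0.5 + 0.20) = 0.32 / 0.70 = 45.7%

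If excessive GWG does not differ by completion, this bias is zero.

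**The case against.** Several points on the other side are sound.

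- A reader might infer that the rule removes all early withdrawers. It does not: one who returned the form stays in. Only women with a single verbal consent and no form are lost, and the article does not say how many.
- The denominator for retention is not fixed. Table 1 takes referral and uptake from administrative data, and withdrawal from medical records plus the programme database, which is not stated to be limited to consenters. Study Design lists consent rates as an outcome, so non-consenters must be counted somewhere. The withdrawal survey carries no consent condition. Reach and uptake therefore need not be affected, and the retention bias arises only if completion and withdrawal are computed on consenters.
- It is not established that the 49 controls include women who never attended. Study Design requires only referral, but Usual Care says the group was provided with face-to-face care and also that appointments were offered.
- Number of calls has no control counterpart, and usual care had no set schedule, so programme completion is not defined for controls.
- The capture rates are assumed. Bias is zero if every non-completer signed, and slightly negative if only completers are missed.

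These points narrow the claim but do not remove it. Study Design still defines the compared group as consenters, the second consent is still tied to completion, and nothing else in the article undoes either.

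**Conclusion.** The difference in entry rules and the completion-linked consent route are explicit in the article. If completion and withdrawal are computed on consenters, LWdP retention is inflated whenever non-completers are captured less often than completers, which the rule makes likely. The size depends on capture rates that the article does not give: about 2.5 to 15 points on a true 60% for form return of 90% down to 50% among non-completers, and none if all of them return it.

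A reader might conclude that the GWG comparison must favour LWdP even if the programme has no effect. The documents do not support that. Selection towards engaged women is to be expected and would favour LWdP if such women gain less weight, but neither the direction nor the size is shown. Nor does restricting the mixed models to women with baseline data create the between-group difference, because those models are within the prospective group.

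The set reported as intention-to-treat is conditional on consent and, for women without a form, on completion. That label claims more than the set can support.

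**What to change.** 1. Compute uptake, withdrawal and completion from aggregate service counts, on the same denominators in both periods: all eligible women referred, and all who attended a first session. State a retention measure that can be applied to both services.
2. Report the number m of women lost for want of a second consent, and give retention bounds that count them as non-completers. If k of the 152 completed, the range is k / (152 + m) to k / 152.
3. For GWG and birth outcomes, compare consented LWdP starters with controls who attended at least one appointment, and show the all-referred control result alongside. This aligns attendance but leaves the second-consent filter in place, so item 2 is still needed.
4. Describe the LWdP set as all consenting participants rather than intention-to-treat.

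The cost is modest. The article places data cleaning and analysis still ahead, and items 2 to 4 need only counts, analysis wording and an attendance flag for controls. Item 1 needs an extraction of aggregate counts. It does not use identifiable records of women who were asked and did not consent, which the waiver described for the retrospective group does not cover. The downsides are a control group smaller than 49 if some never attended, and probably a slightly less favourable retention figure for LWdP.

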### Participants and Referral Pathways

All women aged ≥16 years without pre-exiting diabetes with a prepregnancy BMI >25 kg/m^2^ who are referred for dietetic weight management care during the study period will be eligible for participation. For the purpose of this evaluation, participants must be able to speak and read English sufficiently to allow program participation. Those women who do not meet these criteria will be provided with appropriate face-to-face dietetic care and not participate in this evaluation. Women will be referred into the program by their treating health care provider if they meet these criteria. Alternatively, women meeting these criteria will be able to self-refer into the program through a dedicated program website. Women who are engaged in the program who develop gestational diabetes will be provided the option to remain in the program or withdraw to the hospital’s gestational diabetes model of care.

### Engagement Strategy

Staff will be engaged in the planning phase of LWdP program implementation to identify preferred referral processes for each of the hospital’s 8 different antenatal models of care. This will inform the introduction of an outpatient dietetic referral form for the LWdP program alongside other dietetic services at the facility and the inclusion of the LWdP program referral in paperwork completed during women’s initial booking-in appointment. A program website will be developed to facilitate an online referral pathway, allowing both self-referral and referral by external antenatal health care providers located in the community of women under their care. A consumer engagement survey will be undertaken to inform the flexible program delivery hours, education needs, and topics of interest. Staff from each antenatal model of care will be provided with regular in-services, and the hospital’s media and communications team will be engaged to help build publicity for the program by featuring consumer stories in local newsletters, social media accounts, and local general practitioner communications.

### Screening and Consent

A waiver of participant consent was received as part of the ethics application to retrospectively access routinely collected clinical and administrative data from eligible women in the preimplementation group. For the postimplementation group, all women booked for an initial appointment in the LWdP program will be provided with an electronic link to the participant information sheet and electronic consent form with their participant workbook.

At the commencement of the program, the dietitian counsellor will discuss the evaluation process and answer any questions the participant may have. Program participants who consent to the evaluation will be requested to complete the consent form online in addition to having verbal consent recorded in their health record.

At the completion of the program, participants who verbally agreed to be involved in the evaluation but did not complete the consent form will be reminded to complete this online and a replacement link will be sent if required. Verbal consent will be documented on this second occasion. If no written consent form is received by the time of data analysis but two occasions of verbal consent are documented in the participant’s health record, consent to participate in the evaluation will be considered granted.

### LWdP Program

The LWdP program is aimed at supporting women at high risk of excessive weight gain during pregnancy to achieve GWG within recommendations [2] through the promotion of healthy eating and physical activity. Consistent with Australian dietary guideline recommendations for pregnancy and chronic disease prevention [24], participants will be encouraged to choose whole-grain cereal products, increase fruit and vegetable intake (5 servings of vegetables and 2 servings of fruits per day), choose foods with unsaturated fat, and limit discretionary food choices. They will also be encouraged to focus on eating the right amount of food through portion control and intuitive eating and choosing the right types of foods (minimally processed, low energy density, and high nutrient density). Over the course of the intervention, participants with no contraindications will also be encouraged to gradually undertake pregnancy-appropriate planned physical activity (such as walking, swimming, yoga) to accumulate 150 minutes per week [25]. An additional focus will be on reducing sitting time to contribute to energy expenditure. The goal is for women to track within the target healthy GWG range recommended by the IOM guidelines [2] based on their prepregnancy BMI through changing eating and activity behaviors.

Women referred to the program will be eligible for up to 10 telephone coaching calls over the course of their pregnancy that will usually span a period of 6 months (1 call each week for 1 month, then 1 call every 2 weeks for the next month, then 1 call per month for the next 4 months) and will also receive a participant workbook (Textbox 1). The initial telephone call will be approximately 60 minutes in duration, with subsequent calls lasting approximately 30 minutes, with an emphasis on motivational interviewing [26] and tailored health behavior coaching [27]. The program has been adapted for pregnancy from the Healthy Living after Cancer program [28] and informed by previous formative work with women participating in the New Beginnings Healthy Mothers and Babies study at the same institution [1,20,29,30]. Specifically, the program will target behavioral constructs and consumer experiences gained from prior research with the study population [1,20,29,30]. The intervention is grounded in the social cognitive theory constructs of self-efficacy, social support, and outcome expectancies [31] and emphasizes developing skills using behavior change strategies—goal setting, self-monitoring, identifying potential barriers and problem solving, identifying social support, stimulus control, mindful eating, positive self-talk, and self-reward. The protocol for each call includes an assessment of progress, problem solving, advice/education, collaborative goal setting/goal progression, and development/revision of a behavior-specific action plan. The program topics have been mapped to the refined taxonomy of behavior change techniques [32], as shown in Multimedia Appendix 1.

Living Well during Pregnancy participant workbook content.Introduction to the Living Well during Pregnancy programCoach introduction, scheduling, and discussion of the importance of healthy weight gain in pregnancySection 1: Planning for successParticipant aimsSMART (Specific, Measurable, Achievable, Relevant, and Timed) goal setting and action planProblem solvingTracking tools for eating behaviors, physical activity, weight gain, and meal planningSection 2: What to eat and how muchBenefits of healthy eating and recommendations in pregnancyImportant nutrients (including supplementation)Portion guideSelf-monitoringSection 3: Fat, fiber, and food safetyIncreasing intake of fruits, vegetables, and whole grainsReducing saturated fat intakeFood safetySection 4: Keeping activeSafe exercise during pregnancyPlanning activityPelvic floor exercisesReducing sitting timeSection 5: Healthy pregnancy weight gain and energy balanceEnergy density and food substitutionsStrategies to slow rapid weight gainHealthy snackingSection 6: Meal planning and preparationCreating healthy mealsGrocery shopping planningPlating portion guideStrategies for healthy eating away from homeSection 7: Mindful eatingBreaking the dieting cycleHunger cuesMindful eatingOvereating triggersFood and emotionsSection 8: Celebrating success and planning aheadPlanning aheadPotential obstaclesCelebrating successGetting support from othersHealthy eating during breastfeeding

Accredited Practising Dietitians with experience in providing antenatal care services who have undergone additional training in motivational interviewing will be trained in the delivery of the program. A training manual detailing the program protocol including call transcripts will be provided to all dietitians delivering the program. This additional training includes program philosophy, person-centered care, work shadowing, and the delivery of each call with provision of feedback from the trainer and a checklist of training requirements prior to commencing program delivery. At the completion of each call, the dietitian coach will be required to complete a fidelity checklist to assess the degree to which the call aligned with the protocol.

The program is structured to offer flexibility in the scheduling of call times outside of usual business hours, with early morning and evening times available. Additionally, a caseload continuity of care model will be offered where each participant is allocated one dietitian coach for their pregnancy. Upon booking the first coaching session, each participant will be provided with a welcome letter with information about her coach to assist with establishing rapport.

